### Analysis of the secondary outcomes

Complications will be analyzed with Kaplan-Meier curves and the log-rank test. The comparison of the view of the glottis will be analyzed using the Wilcoxon rank-sum test. Logistic regression and Cox regression will be used to explore the effect of additional explanatory variables.

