**Methods:**

The JuniorDoc-VL Trial is a randomized, controlled, patient-blinded clinical trial of novice anesthesiology residents trained in DL and VL. Thirty residents will be randomly assigned to either the intervention group (VL group) or the control group (DL group) with a 1:1 allocation. The first-pass-success (FPS) rates (primary endpoint) and complication rates (secondary endpoint) will be compared between groups.

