Residents record the number of attempts and the techniques employed for tracheal intubation on the case report form (CRF) immediately following the airway management procedure. Each intubation was supervised by an experienced board-certified consultant anesthesiologist, ensuring adherence to safety standards and providing immediate guidance when necessary. An attempt to secure the airway was defined as the insertion of the laryngoscope blade into the mouth, details are shown in Table 1. In accordance with the internal hospital protocol, residents are required to consult an anesthesiologist specialist following two unsuccessful attempts. In accordance with this protocol, the participants in the present study will be replaced by the consultant or instructed by him following two unsuccessful attempts. In the event of any safety-critical situations arising (e.g., desaturation, severe hypotension, airway injuries, or if the consultant deems it necessary), the intubation by the resident will be aborted. The number of subsequent attempts made by this clinician to successfully secure the airway was also recorded on the case report form (CRF). No specific training is provided prior to the use of either intubation method. In accordance with our internal standard, the participants receive a brief introduction to the medical devices and their correct use according to the manufacturer's instructions as part of the on-boarding process. This is also required by medical legislation in Germany.

**Table 1 Tab1:** Definition of the important outcome variables

First-Pass-Success	Desaturation	Hypotension
The initial tracheal intubation attempt was defined by the insertion of a laryngoscope blade and/or tracheal tube into the patient’s mouth		
The initial intubation attempt was considered to have failed if it did not result in successful endotracheal intubation, with or without an attempt to pass the tube	<90% O_2_saturation if not pre-existing and without a prescribed time period	< 65 mmHg mean arterial pressure (MAP) if not pre-existing and without a prescribed time period
Subsequent attempts at intubation were characterized by the reinsertion of an endotracheal tube or the insertion of the same or a new laryngoscope blade	So a single valid measurement <90% is documented with the term “desaturation”	

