#### Intervention group

From the first week of clinical activity, the intervention group performs video laryngoscopy with a hyperangulated blade as the standard method for every ETI. They are supervised by a board-certified anesthetist during each induction of general anesthesia. Following the completion of 200 ETI procedures by each resident within their randomized group (VL), the evaluation was concluded. For each ETI, residents indicated whether the following difficulties were present. Furthermore, the residents were asked to indicate whether any of the following complications had occurred in the case of each ETI. In addition, the rate of complications in both groups will be monitored by the study team.

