### Outcomes {12}

Study participants will independently document various parameters on the case report form (CRF) immediately after tracheal intubation or, at the latest, shortly thereafter. Any complications arising during the procedure will be recorded no later than after extubation. This approach ensures that the documentation is provided in a timely manner and is directly related to the case.

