## Statistical methods

### Statistical methods for primary and secondary outcomes {20a}

A parallel two-group design will be used to test whether the Group 1 mean is different from the Group 2 mean (H0: μ1 − μ2 = 0 versus H1: μ1 − μ2 ≠ 0). The comparison will be made using a two-sided, two-sample equal-variance t-test, with a Type I error rate (α) of 0.05. The common standard deviation for both groups is assumed to be 10. The distribution of the data of the primary endpoint (FPS) is tested for normality using the Shapiro-Wilk test. In addition, graphical methods such as histograms and Q-Q plots are used to visually assess the distribution of the data. To compare FPS values between groups, either the parametric t-test (for normally distributed data) or the non-parametric Mann-Whitney U-test (for non-normally distributed data) is used, depending on the distribution. The choice of test was made based on the results of the normality test. Multiple logistic regression analysis of subgroup factors will allow us to assess the factors affecting FPS when comparing DL with VL, such as age, sex, ASA, BMI and provider experience. Cox regression can be used to evaluate the combined impact of the method and other explanatory variables. We used the following software for the calculation PASS 2024 Power Analysis and Sample Size Software (2024). NCSS, LLC. Kaysville, Utah, USA.

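### Complications are recorded as yes/no per intubation, but the plan tests them with Kaplan-Meier and log-rank methods, which either ignore clustering by resident or count only each resident's first event

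*Protocol article*

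**What the plan says.** **Method.** *Analysis of the secondary outcomes* is unconditional: "Complications will be analyzed with Kaplan-Meier curves and the log-rank test". It then adds: "Logistic regression and Cox regression will be used to explore the effect of additional explanatory variables". The section on primary and secondary outcomes {20a}, which deals mainly with first-pass success, says: "Cox regression can be used to evaluate the combined impact of the method and other explanatory variables".

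**Data.** *Intervention group* describes a yes/no record: "the residents were asked to indicate whether any of the following complications had occurred in the case of each ETI". Table 1 defines desaturation and hypotension as thresholds crossed "if not pre-existing and without a prescribed time period", and for desaturation adds: "So a single valid measurement <90% is documented with the term" desaturation. *Outcomes {12}* sets a deadline for documentation: "Any complications arising during the procedure will be recorded no later than after extubation". Each resident is followed for 200 ETIs in either arm, so 30 residents give 6,000 ETIs.

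**Target.** The abstract's Methods paragraph says that "complication rates (secondary endpoint) will be compared between groups".

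**The concern.** Kaplan-Meier and log-rank methods need a time origin, a time scale, an event time for each unit and a censoring rule. The article gives none of these for complications. The recording limit at extubation says when the form must be complete, not when the event occurred. *Plans for assessment and collection of outcomes {18a}* mentions time points for recruitment and intervention only.

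The method can therefore be carried out in two ways, and each has a defect. With the ETI as unit, 6,000 correlated observations are treated as independent. With the resident as unit and ETI number as time, repeat complications are dropped and the quantity compared is time to first complication, not a rate. The abstract and discussion hypothesise that video laryngoscopy lowers complication rates. At stake is either a false-positive claim on that hypothesis or a test too weak to support it.

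**Working it through.** The article gives no complication rate, no between-resident spread and no power for complications (its one power figure concerns the primary endpoint), so there is no plan figure to reproduce.

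**Inputs from the article:** 30 residents, 15 per arm; 200 ETIs each; 6,000 ETIs in all. Two-sided 0.05 is stated for the primary test and is used here too.
**Assumptions:** complication rates per ETI of 0.25% to 10%; resident random intercept with SD 0 to 0.5 on the logit scale. The simulations ran at least 2,000 trials per setting, so results carry an uncertainty of about ±0.02.

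**Reading 1: the ETI is the unit and all times are equal.**
There is one event time, with d events among n = 6,000 ETIs, of which n1 = 3,000 are in one arm.
- Kaplan-Meier: S = 1 − d/n, so 1 − S = d/n, which is the complication proportion. The estimate is right.
- Log-rank: (O1 − d·n1/n)² / V, with V = d(n1/n)(1 − n1/n)(n − d)/(n − 1). This is the Pearson 2x2 chi-square times 5,999/6,000.
- The variance V ignores the resident. The design effect is 1 + 199 × ICC. For a 10% rate and a between-resident coefficient of variation of 0.3, ICC = 0.03²/(0.10 × 0.90) = 0.01 and the design effect is 2.99. The type I error is then about 2[1 − Φ(1.96/√2.99)] = 2[1 − Φ(1.13)] ≈ 0.26; simulation of that setting also gives 0.26.

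Simulated type I error with the logit-SD model (nominal 0.05; blank = not run):

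| Rate | SD 0 | SD 0.2 | SD 0.3 | SD 0.5 |
|---|---|---|---|---|
| 10% | 0.055 | 0.13 | 0.23 | 0.40 |
| 5% | | | 0.16 | 0.29 |
| 2% | | | | 0.18 |
| 1% | | 0.06–0.07 | | 0.12 |

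**Reading 2: the resident is the unit and ETI number is the time.**
Only first events count. With a common rate p and no spread, expected events are 6,000p, and events used are 30[1 − (1 − p)^200].

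| p | All events | Used | Discarded |
|---|---|---|---|
| 0.5% | 30 | 19.0 | 37% |
| 1% | 60 | 26.0 | 57% |
| 2% | 120 | 29.5 | 75% |
| 5% | 300 | 30.0 | 90% |
| 10% | 600 | 30.0 | 95% |

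With at most 30 events, Schoenfeld's formula gives power Φ(|ln HR|·√(30/4) − 1.96). For HR 0.5 this is Φ(0.693 × 2.739 − 1.96) = Φ(−0.06) ≈ 0.48. For 80% power, 4(1.96 + 0.84)²/0.693², or about 66 events, would be needed.

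Simulated power at SD 0.5, against a Welch test on the 30 resident-level proportions:

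| Rates | Log-rank, first event | Resident proportions | Events discarded |
|---|---|---|---|
| 10% vs 6% | 0.25 | 0.72 | 94% |
| 5% vs 2.5% | 0.36 | 0.82 | 87% |
| 2% vs 1% | 0.36 | 0.64 | 70% |
| 1% vs 0.5% | 0.29 | 0.42 | 52% |
| 0.5% vs 0.25% | 0.23 | 0.27 | 36% |

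The type I error of this log-rank test stayed at 0.05 to 0.06, so Reading 2 is valid but inefficient. A different model of spread (coefficient of variation 0.3) points the same way: 0.16 against 0.68 at 10% vs 7%.

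**The case against.** **A time axis exists.** ETI number runs from 1 to 200 with a fixed end, withdrawal could serve as censoring, and learning curves are a declared interest. An analysis plan could declare this scale, so a reader who infers that the analysis is undefined goes too far. This stands. However, declaring the scale would not recover repeat events, nor turn time to first complication into the rate named in the abstract.

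**The ETI-level version estimates the right quantity.** This also stands. A reader might infer that neither version yields the complication rate, but Kaplan-Meier at one common time gives exactly that proportion. The defect there is the standard error.

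**The size depends on unseen inputs.** This stands too. With little resident variation or rare events the inflation is slight, and with none it vanishes. For a rare single complication the first-event test loses little power. The article lists desaturation, regurgitation and dental or soft tissue trauma as examples, without a composite, so some could be rare.

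**Logistic regression is already listed, and Cox is optional.** This is partly right. Cox is permissive in {20a} and exploratory among the secondary analyses, so it should not be read as the planned group comparison. But logistic regression is likewise offered only for additional explanatory variables. It does not replace the log-rank comparison, and no allowance for residents is stated.

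**Conclusion.** The point holds as a mismatch between a fixed method and the endpoint as recorded, not as missing detail. As written, the test either ignores the unit of randomisation (type I error about 0.07 to 0.40 for rates of 1 to 10% and SD 0.2 to 0.5) or uses at most 30 first events. In the second case the cost ranges from small (power 0.23 against 0.27, about 36% of events dropped, at 0.5% vs 0.25%) to large (0.25 against 0.72, 94% dropped, at 10% vs 6%). All rates and SDs are assumptions.

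Two stronger inferences are not supported. That nearly all information is lost is true only for frequent complications. That this is the main secondary analysis rests on the abstract naming only complications; *Secondary outcome measure* lists several outcomes without rank. Severity is should-fix: the endpoint is secondary and the primary first-pass-success comparison is untouched.

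**What to change.** In *Analysis of the secondary outcomes*, replace Kaplan-Meier and log-rank as the between-group test of complications with one of two analyses, named in advance:
- a comparison of resident-level complication proportions (15 against 15); or
- a logistic model per ETI with arm and a random resident intercept.

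Report the risk difference or odds ratio with a 95% confidence interval. Where the outcome is binary per ETI, replace Cox regression in that section and in {20a} by the same clustered logistic model. Curves over ETI number may stay as a descriptive display, with the time scale stated.

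The cost is wording in two paragraphs. No new data are needed, since the per-ETI form linked to the resident already holds what these analyses use.

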### Interim analyses {21b}

No interim analyses are pre-planned.

### Methods for additional analyses (e.g., subgroup analyses) {20b}

Where appropriate, we will perform a separate analysis by type of surgery (e.g., general surgery, bariatric surgery) for patients with difficult intubation, defined as more than two attempts.

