### Trial design {8}

The JuniorDoc-VL study is a randomized, controlled, patient-blinded trial of novice anesthesiology residents (< 1 month) trained in conventional DL and VL. The study design is illustrated in Fig. 1. The participating residents (*n* = 30) are randomly assigned 1:1 to either the DL group (control group) or the VL group (intervention group). Residents are allocated to one of the two groups once at the start of their clinical work in anesthesiology. This signifies that the overall study can be evaluated on the basis of 6.000 ETIs, which represents a significant sample size. The principal aim of this trial is to demonstrate that the experimental treatment (VL) is superior to the control (DL).

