#### Subgroups

Demographics: patients (age, gender, body mass index (BMI))American Society of Anesthesiologists (ASA) class.Analysis of care providers (clinical experience, training status, and experience in direct and indirect laryngoscopy)Type of procedure (e.g., general surgery, bariatric surgery).

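### No stated analysis tests whether the VL effect on first-pass success differs between subgroups, and the per-surgery analysis is confined to intubations whose first attempt failed

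*Protocol article*

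**What the plan says.** The article's Subgroups list covers patient demographics, ASA class, type of procedure and care-provider characteristics: "Analysis of care providers (clinical experience, training status, and experience in direct and indirect laryngoscopy".

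Two analyses are attached to these factors.

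- Section {20b}, where appropriate: "we will perform a separate analysis by type of surgery (e.g., general surgery, bariatric surgery"), with the restriction "for patients with difficult intubation, defined as more than two attempts".
- Section {20a}: "Multiple logistic regression analysis of subgroup factors will allow us to assess the factors affecting FPS when comparing DL with VL", with age, sex, ASA, BMI and provider experience as the examples.

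No arm-by-factor interaction is named anywhere, and none is excluded. The regression is described without a resident term. Residents are the randomised units: they "are randomly assigned 1:1 to either the DL group (control group) or the VL group (intervention group", 30 in all, and each contributes 200 intubations.

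**The concern.** A subgroup question in a comparative trial asks whether VL minus DL differs between kinds of patient. Separate analyses by surgery type do not test that difference. Coefficients for BMI or ASA in a regression without interactions describe prognosis, not for whom VL helps more.

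The restriction in {20b} adds a second problem. An intubation with more than two attempts has already failed its first attempt under Table 1, so the primary outcome is constant in the subset. Entry to the subset also depends on the outcome of the randomised technique, so the VL and DL patients inside it are no longer comparable.

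At stake is the patient-subgroup question, which the design can address for common patient factors and which the stated methods leave unanswered. The primary comparison of resident-level FPS is not affected.

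**Working it through.** **The plan's own figure.** The article gives no precision for any interaction. Its only related figure is the power of 0.66262 for the main effect (Sample size {14}). A difference of 10, SD 10 and 15 residents per arm give a noncentrality of 10/3.65 = 2.74 on 28 df, and power 0.753 by the exact t calculation. The printed value matches a difference of 9 with SD 10, or equivalently a difference of 10 with SD 11.11. That is a separate issue. With SD 11.11 the main-effect standard error (SE) would be 11.11 × √(2/15) = 4.06, which would not weaken what follows.

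**Inputs.** From the article: SD 10 points for resident-level FPS ({20a}), 15 residents per arm, 200 intubations each (3,000 per arm), DL rate 80% ({14}). Assumed: VL rate 90%, to match the stated 10-point difference (the article also quotes 92–94%); equal category shares across residents.

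**1. What the {20b} subset can show.** More than two attempts means the first attempt failed, so FPS = 0 in both arms and VL minus DL on FPS is 0 − 0 in every surgery type.

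Selection: as an illustration only, suppose the first and second attempts fail independently at 20% (DL) and 10% (VL). Then about 3,000 × 0.04 = 120 DL and 3,000 × 0.01 = 30 VL intubations have two failures. A working VL effect would itself unbalance the subset.

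Other outcomes: the article does not give the subset's share s. For an assumed s of 0.5–5% (30–300 intubations), a 50/50 surgery split and an outcome rate p of 10–50%, interaction SE = √[4p(1−p)/(1500s)]:
- s = 5%, p = 10%: √(0.36/75) = 6.9 points
- s = 0.5%, p = 50%: √(1/7.5) = 36.5 points

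**2. Main effect.** SE = 10 × √(2/15) = 3.65 points.

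**3. Arm-by-patient-factor contrast over all intubations.** At 200 intubations the binomial SD of a resident's rate is √(0.8×0.2/200) = 2.8 points (DL) and √(0.9×0.1/200) = 2.1 points (VL). An SD of 10 is therefore mostly between-resident variation (about 9.6–9.8 points), and this cancels within residents. With smaller-category share q, and τ the between-resident SD of the factor's effect:

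SE² = [(0.16 + 0.09)/3000] × [1/q + 1/(1−q)] + 2τ²/15

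| q | τ = 0 | τ = 5 | τ = 10 |
|---|---|---|---|
| 50% | 1.83 | 2.58 | 4.08 |
| 20% | 2.28 | 2.92 | 4.31 |
| 10% | 3.04 | 3.55 | 4.75 |
| 5% | 4.19 | 4.57 | 5.56 |

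A simulation with τ = 0 gave 1.83 at q = 50% and 3.00 at q = 10%. With VL at 92–94% the 50/50 figure falls slightly, to 1.76–1.70.

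Break-even with 3.65: at τ = 0, q(1−q) = (0.25/3000)/(0.0365²) = 0.0625, so q = 6.7%. At q = 50% the limit is τ = √[(13.33 − 3.33) × 15/2] = 8.7 points. At q = 10% it is √[(13.33 − 9.26) × 15/2] = 5.5 points.

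**4. Arm-by-provider factor.** With 7 and 8 residents per cell, SE = 10 × √(2/7 + 2/8) = 7.3 points, twice the main-effect SE.

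**5. Leaving out the resident term.** Treating 6,000 intubations as independent gives an arm SE of √(0.25/3000) = 0.91 points, a quarter of 3.65. For a provider factor split in half it gives 2 × 0.91 = 1.83 instead of 7.3.

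**The case against.** The strongest reply is that this is exploratory wording in a condensed article. The regression is said to assess factors in the comparison of DL with VL, which could be meant to include arm-by-factor terms, and exact model terms are commonly left to an analysis plan. That is fair: the missing interaction term in {20a} would be a weak point taken alone. It does not rescue {20b}, which fixes both a method and a population, and an analysis plan that followed it could not estimate any VL effect on FPS by surgery type.

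Three stronger readings are tempting and are not supported.

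- A reader might infer that the plan will produce false claims that VL improves FPS in one surgery type and not in another. It cannot do so from the {20b} subset, where FPS is constant. Rates of discordant results from separate FPS tests over all intubations would describe an analysis the article does not plan, with strata it does not name, so none is given here.
- A reader might infer that interactions are in general estimated better than the main effect. This fails for provider factors, for rare categories, when τ is large, and in the {20b} subset. A smaller SE is also not more power, because true interactions are often smaller than the main effect.
- A reader might infer that the provider factors ("clinical experience, training status, and experience in direct and indirect laryngoscopy") cannot vary, since all entrants have under one month of service. That limit concerns service in this department. Section {11a} collects earlier intubations, which may differ between residents. What does stand is that no resident switches arm ({16a}), so technique-specific experience gained in the trial largely reproduces the arm.

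**Conclusion.** The concern holds in a bounded form. No stated analysis, read as written, tests whether the VL effect on FPS differs between the listed subgroups. The per-surgery analysis in {20b} conditions on a post-randomisation result and cannot estimate an FPS effect at all. The regression in {20a}, read plainly, gives prognostic effects and ignores clustering; without a resident term, SEs for the arm effect and for provider-level interactions would be about four times too small.

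For common patient factors the trial can estimate the interaction with an SE of about 1.8 to 3.0 points, against 3.65 for the main effect. This rests on the planned SD of 10, rates of 80% and 90%, similar case mix across residents, a smaller category above about 7% of intubations, and modest τ (below about 8.7 points at a 50/50 split, 5.5 at 90/10). The article gives neither category shares nor τ. For provider experience, an SE of about 7.3 points makes any interaction estimate very imprecise.

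**What to change.** In {20a} and {20b}, for the subgroup question:

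- Name the patient factors (BMI, ASA class, surgery type) and their categories in advance.
- Fit one model per factor over all intubations, with arm, factor and arm-by-factor terms and resident as random effect, adding a random factor slope where it can be estimated. State whether the interaction is on the percentage-point or odds-ratio scale.
- Report the interaction with its 95% confidence interval, and show stratum effects only beside it.
- Keep any summary of intubations with more than two attempts descriptive.
- Define provider experience as the pre-randomisation intubation count from the form in {11a}, and label that interaction as low precision.

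The cost is revised wording and a little more analysis work, with no new data. The change does alter the population of the {20b} analysis, from the more-than-two-attempts subset to all intubations, and the amendment should say so.

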#### Primary outcome measure

Successful tracheal intubation on the first attempt (Table 1).

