#### Secondary outcome measure

Complications such as oxygen desaturation below SpO_2_ 90%, regurgitation, and dental or soft tissue trauma.Number of attempts made during laryngoscopy.The level of training with intubation success.Any failures or transitions to other rescue techniques.The use of OELM techniques such as BURP, CP, or adjustment of the participant's head and neck position.When using VL, record the occurrence of fogging and assess the glottic view using the Cormack-Lehane classification and the Percentage of Glottic Opening Score.Indications of difficult airway management (e.g., Mallampati Score, limited mouth opening)

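### Difficult intubation is defined by the number of attempts, an outcome of the assigned device, so this subset should not be used to compare VL with DL

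*Protocol article*

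**What the plan says.** Under *Methods for additional analyses {20b}*, the protocol states that, where appropriate, "we will perform a separate analysis by type of surgery (e.g., general surgery, bariatric surgery"), and restricts this to a subset: "for patients with difficult intubation, defined as more than two attempts". It names no endpoint for this analysis and does not say whether the two arms are to be compared within the subset.

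Three other places bear on the definition:

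- *Secondary outcome measure* lists "Number of attempts made during laryngoscopy" as an outcome. The same list includes "Indications of difficult airway management (e.g., Mallampati Score, limited mouth opening"), so markers of difficulty are recorded separately from the attempt count.
- Table 1, under *Intervention description {11a}*, sets the rule for the primary endpoint: "The initial intubation attempt was considered to have failed if it did not result in successful endotracheal intubation". It also says what counts as a further attempt: "Subsequent attempts at intubation were characterized by the reinsertion of an endotracheal tube or the insertion of the same or a new laryngoscope blade".
- *Intervention description {11a}* says that the trial deliberately includes patients with an expected difficult airway as well as those without. A concept of difficulty that precedes intubation therefore exists in the protocol, but {20b} does not use it.

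**The concern.** A subgroup supports a fair comparison of randomised arms only if membership is settled before the assigned intervention can act. Here membership is settled by how the intubation went. The trial's hypothesis is that VL raises first-attempt success, so the device is expected to change who enters the subset. VL and DL patients inside it would then differ in case mix even if the arms were perfectly balanced at the outset.

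A comparison of complications or glottic view in this subset could be read as evidence on how the devices perform in difficult airways. It would not be that. It would compare two differently selected sets of failures, and it sits badly with the intention-to-treat principle stated in {20c}.

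**Working it through.** The section states no figure for this analysis, so there is none to reproduce. The check has three steps.

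**1. FPS within the subset (definitions only).** More than two attempts means at least three. A third attempt requires the first and second to have failed. By Table 1 the first attempt is then a failure. FPS in the subset is 0% in both arms, whatever the true success rates, and no assumption is needed.

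**2. Size of the subset by arm.** Inputs:

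- assumed FPS of 80% for DL and 92-94% for VL (*Sample size {14}*);
- 15 residents per arm at 200 intubations each, so 15 × 200 = 3,000 per arm, consistent with the 6,000 total in *Trial design {8}*.

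Assumptions not in the protocol: attempts are independent with a constant success rate p, and every patient with two failures goes on to a third attempt. Then P(more than two attempts) = (1 − p)².

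| Arm | p | (1 − p)² | Of 3,000 |
|---|---|---|---|
| DL | 0.80 | 0.20² = 4.0% | 120 |
| VL | 0.92 | 0.08² = 0.64% | 19.2 |
| VL | 0.94 | 0.06² = 0.36% | 10.8 |

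The DL subset is 120/19.2 = 6.25 to 120/10.8 = 11.1 times the VL subset. Some 11 to 19 VL cases would then be divided by type of surgery.

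**3. Case mix within the subset (illustration).** Suppose 20% of patients in each arm are truly difficult. Let per-attempt success in easy and difficult patients be 90% and 40% with DL, and 95% and 80% with VL. These values are assumed. They return overall FPS of 0.8 × 0.90 + 0.2 × 0.40 = 80% for DL and 0.8 × 0.95 + 0.2 × 0.80 = 92% for VL.

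- DL: 0.8 × 0.10² + 0.2 × 0.60² = 0.008 + 0.072 = 8.0% (about 240 of 3,000). Truly difficult share: 0.072/0.080 = 90%.
- VL: 0.8 × 0.05² + 0.2 × 0.20² = 0.002 + 0.008 = 1.0% (about 30 of 3,000). Truly difficult share: 0.008/0.010 = 80%.

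Arms that start with the same 20% end at 90% and 80% in the subset. With the baseline share fixed, the difficult share in the subset depends only on the ratio of the failure rate in difficult patients to that in easy patients. Here that ratio is 0.60/0.10 = 6 for DL and 0.20/0.05 = 4 for VL. If VL instead raised the ratio, the imbalance would run the other way. The protocol gives nothing that settles which applies.

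For contrast, FPS among the patients who were difficult at baseline would be 40% with DL and 80% with VL in this illustration. A definition fixed beforehand can show a difference that the attempt-based definition cannot.

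**The case against.** The strongest reply is that {20b} names neither FPS nor a comparison of arms. Type of surgery is the only stratifier it mentions. A pooled description of difficult cases by surgery, or their frequency by surgery, would be legitimate and fits the words. This stands in part: an arm comparison is an inference from the subgroup heading and from the restriction to a subset. Even so, the sentence needs to say which is meant.

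A reader might infer more than the documents support:

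- *That VL will look worse because only its hardest cases remain.* The illustration gives the opposite imbalance, and both results rest on assumed rates. Only a bias of unknown direction can be claimed.
- *That the subset fails because later attempts are not the resident's unaided work.* The resident "will be replaced by the consultant or instructed by him following two unsuccessful attempts", but every intubation in the trial is supervised with guidance available, so unaided skill is not what is measured anywhere. This is not a separate defect of {20b}.
- *That the trial set out to test VL in difficult airways and has lost that test.* The stated objective is overall FPS among first-year residents. Expected difficult airways are included so that the patients are representative.

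It is also fair to say that the recorded difficulty indicators are imperfect. They are listed among the secondary outcomes, and residents who know their arm complete the form after intubation.

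**Conclusion.** The point holds in a limited form. Difficult intubation as defined in {20b} is an outcome of the randomised device and is unsuitable as a subgroup for comparing arms. If arms are compared there, the 0% FPS follows from the definitions alone, and other contrasts lose the protection of randomisation.

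The size of the imbalance is conditional. It is about 120 DL against 11 to 19 VL intubations under independent attempts at the protocol's assumed rates, and about 240 against 30 in the illustrative mixture. Neither is a forecast.

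Severity is minor to moderate. This is one additional analysis, to be done only where appropriate, and the primary endpoint and its test are untouched.

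**What to change.** 1. Report more than two attempts as an outcome by arm over all intubations, and by type of surgery if wanted. State that it will not define a subgroup for comparing arms.
2. If a difficult-airway subgroup is wanted, define it before analysis from indicators assessed before laryngoscopy, such as Mallampati score and limited mouth opening. Take these from the pre-operative assessment where possible, because the unblinded resident completes the case report form after the event.
3. Examine the arm-by-predicted-difficulty interaction in the logistic regression for FPS already planned under *Statistical methods {20a}*, allowing for repeated intubations by the same resident. That section does not state such an allowance, so this part goes beyond rewording {20b}.

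Item 1 costs a sentence and no new data. Items 2 and 3 add a little analysis work, may require reading the pre-operative record, and accept that such indicators predict difficulty imprecisely.
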